### Sample selection

The directors and care service coordinators of each health center will be duly informed about the trial, and they will be asked for their availability as well as their consent to take part in the trial. Nursing staff of each health center who so desire will be able to take part, being in such case responsible for the research study implementation and follow-up in their respective health center.

Records of patients included in the nursing at home program for immobilized patients will be assessed to determine whether patients comply with the inclusion requirements. At this point, such patients will sign the informed consent form and subsequently, their details will be randomized by a computer system independent of the professional staff, which will be processed at the clinical trial control center.

To achieve a power rate of 80.00% to reject the null hypothesis (*H*_0_: the difference between proportions *p*1 and *p*2 is lower than the noninferiority bound), using a normal asymptotic analysis test (noninferiority), unilateral proportions for two independent samples, taking into account that the level of statistical significance is 5.00%, and assuming that the proportion in the reference (control) group is 45.00% and the proportion in the experimental group is 45.00% [9], the proportion of experimental units in the reference group is 50% related to the total and the noninferiority bound (delta) is 10.00%, then, it will be necessary to include 306 experimental units in the reference group and 306 units in the experimental group, totalling 612 units in the study. Taking into account that the expected withdrawal rate is 15.00%, it will be necessary to enroll 360 experimental units in the reference group and 360 units in the experimental group, totalling 720 experimental units in the trial.

The main outcome will be the incidence of grade 2 pressure ulcers in patients during the 16-weeks of follow-up (112 days). We have selected this grade because when the patient has grade 2 pressure ulcers, prevention can no longer be carried out, and prevention is the intended outcome. We are only able to conduct this trial on intact skin, therefore it is only possible to conduct the trial when the patients have no pressure ulcer or have grade 1 pressure ulcers, when there are just erythemas. Therefore, patients who develop grade 2 pressure ulcers with breaks in the skin are excluded from the trial, as we cannot keep using the products because prevention is not useful anymore. Such patients will be treated again by the nurse who will cure the pressure ulcer, although this will be done out of the trial. When preventing the patient from developing grade 2 pressure ulcers, we are also preventing greater stages of ulcer. The 112 days of follow-up are higher than trials carried out up to now, 7 days [21], 9 days [24], and 30 days [25], which is more than enough for the appearance of pressure ulcers at any stage. The appearance of grade 2 pressure ulcers will be confirmed by the inspection of those areas where the product has been applied (sacrum, hips, and heels).

As secondary endpoints, cost measures will be applied that will allow us to assess the cost-effectiveness balance of the new product (olive-oil formula) against the HOFA-based products. As inputs of this model, the cost of each treatment will be used and defined as the number of units (NE_*ij*_) necessary to carry out 16 weeks’ treatment (112 days) multiplied by the price of one unit (*P*_*i*_ and *P*_*j*_) (the price of each unit will be achieved from the information provided by each supplier according to the market price). The number of units will be the result of dividing the treatment period (DT_*ij*_) (112 days) by the number of days (*d*_*ij*_) the recipient used, according to the dose established in the trial protocol in each branch of the treatment. The resulting amount achieved shall be rounded up, even if the whole number of units has not been fully used:

$${\mathrm{NE}}_{\mathrm{ij}}={\mathrm{DT}}_{\mathrm{ij}}/d_{\mathrm{ij}}$$

As a variable cost, the number of visits of the nurse to the patient’s home during the trial period (VE_*i*_) will be used, which will act as a proxy measure of the level of care required. The mean time spent on each visit will be estimated according to the standard value of time within the community-health nurse working hours spent during a nursing care at home visit (this information will be obtained from the human resources management divisions of the different health districts and an assessment test will be carried out on the length of 30 visits to patients with the characteristics complying with the inclusion criteria, randomly selected among the health centers included in the study, prior to the commencement of the trial). Structural fixed costs will not be included, as in all cases the care assistance is provided at the patient’s home and the services are already included in the aforementioned variable. It will not be possible to assess the cost derived from the family care, since this is quite difficult to achieve and has a high variability. Therefore, this will not be included in the model. In those cases when there is a remunerated caregiver, such cost will not be included in the total costs either, as it would create a bias in the estimation when comparing them with those patients who are not assisted by a remunerated caregiver. Furthermore, the intangible costs derived from certain aspects, such as the pain level derived from the process will not be included either. Therefore, the estimation of total costs (CT) in the model will remain as follows:

$${\mathrm{CT}}_{\mathrm{ij}}={\mathrm{NE}}_{\mathrm{ij}}+{\mathrm{VE}}_{\mathrm{ij}}{}_{.}$$

The effectiveness variable will be the appearance of pressure ulcers. A limited number of states will be taken into account: appearance of pressure ulcers (*U*_1_) and nonappearance of pressure ulcers (*U*_0_). The incidence will be estimated in percentages, which will be used for the incremental estimations on cost-effectiveness.

Furthermore, variables on characterization of patients and caregivers will be included to assess sociodemographic data, such as the time registered in the care service for immobilized patients, information about previous cases of pressure ulcers, comorbidity, nutritional and cognitive status, and dampness (incontinence), apart from taking into account the ulcer location as well as the availability of technical support items (mattress and cushions to avoid bedsores, adjustable beds, and so on). With regard to the caretaker, the age, sex and whether he or she is a family or remunerated caregiver will be taken into account.

A basal-assessment will be performed on all patients at the beginning of the trial and this will be repeated each week up to the conclusion of the follow-up period, or until a pressure ulcer appears in patients. All the information concerning the application of the products will be registered in the weekly evaluations.

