#### Statistical analysis

Initially, a descriptive analysis of the variables included in the trial will be performed. Continuous variables will be summarized with mean, standard deviation, median, and interquartile range. Categorical variables will be shown in absolute and relative frequencies. An analysis of the normal distribution by the Kolmogorov-Smirnov test, symmetry analysis, and kurtosis will be performed.

With the aim of assessing the noninferiority of the olive oil for the prevention of pressure ulcers, a contrast of association between the appearance of pressure ulcers and the kind of treatment received (olive-oil-based cream or conventional treatment) will be carried out, by absolute and relative measures of effect sizes (complete reduction of risk, number needed to treat, relative risk, and relative reduction of risk), with their respective confidence intervals at 95%. It will be determined whether the confidence interval includes the estimated delta value from the sample or not, so as to reject or accept the null hypothesis.

A bivariate analysis will be carried out using the Student’s t and chi-squared tests according to the characteristics of the variables analyzed in the event that these are normally distributed. Otherwise, nonparametric tests will be applied, such as the Wilcoxon and Man-Whitney U tests. Likewise, analysis of variance (ANOVA) will be applied for the association of quantitative and qualitative variables in the necessary cases, as well as robust measures of central tendency in cases of homoscedasticity (which will be tested by Levene’s test) by means of the Welch and Brown-Forsythe test.

An analysis according to the Kaplan-Meier curves and log-rank test will be carried out to determine the progress of the appearance of pressure ulcers in both groups, taking into account the treatment applied, the sex, age, nutritional status, and functional degree of the patient and the caregiver’s age.

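### The sample size assumes a one-sided 5% test, but noninferiority is judged on 95% confidence intervals; 612 evaluable patients then give about 70% power, not 80%

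*Protocol article*

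**What the plan says.** **Sizing (Protocol article, Sample selection).** The calculation starts "To achieve a power rate of 80.00% to reject the null hypothesis". It specifies "unilateral proportions for two independent samples, taking into account that the level of statistical significance is 5.00" percent, "assuming that the proportion in the reference (control) group is 45.00" percent, "the proportion in the experimental group is 45.00" percent, and "the noninferiority bound (delta) is 10.00" percent. The result is "306 experimental units in the reference group and 306 units in the experimental group, totalling 612 units in the study", raised to 360 per arm (720 in total) for 15% withdrawal.

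**Decision (Protocol article, Statistical analysis).** Noninferiority is assessed through absolute and relative effect measures "with their respective confidence intervals at 95" percent. The null hypothesis is then rejected or accepted according to whether the interval includes delta. Later in the same section the rule of interval against delta is repeated for the main outcome, and the per-protocol analysis is made the main one.

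The article mentions neither a 90% interval nor a one-sided 95% bound.

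**The concern.** A noninferiority test at one-sided level α corresponds to a two-sided interval of level 1 − 2α. One-sided 5% goes with a 90% interval, and a 95% interval goes with one-sided 2.5%. The article takes its sample size from the first pairing and its decision rule from the second.

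Two things follow. First, the stated 80% power does not describe the stated analysis, so the chance of failing to show noninferiority when the products are truly equal is larger than planned. Second, the same data can pass under one section and fail under the other. While this is open, the error level of the main claim (2.5% or 5%) could be settled after the results are known.

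**Working it through.** **Inputs, all from Sample selection:** incidence p = 0.45 in both arms (true difference 0), margin δ = 0.10, 1:1 allocation, power 80% (z = 0.8416), one-sided α = 5% (z = 1.645), withdrawal 15%. The 95% level (z = 1.96) comes from Statistical analysis.

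**1. Reproduce the article's figure.**

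n per arm = (z₁₋α + z₁₋β)² × 2p(1 − p) / δ²

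- One-sided 5%: (1.645 + 0.8416)² × 0.495 / 0.01 = 306.04, matching the stated 306. Then 306 / 0.85 = 360, also as stated.
- One-sided 2.5%: (1.96 + 0.8416)² × 0.495 / 0.01 = 388.5, so 389.

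Using null rates of 40% and 50% for the variance in the test term gives 304 and 386 respectively. Under either formula, only one-sided 5% reproduces the stated size.

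**2. Power of the stated size under each decision rule.**

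Power = Φ( δ / √(2p(1 − p)/n) − z₁₋α )

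At n = 306 the standard error is √(0.495/306) = 0.0402, and 0.10/0.0402 = 2.486. At n = 360 it is √(0.495/360) = 0.0371, and 0.10/0.0371 = 2.697.

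| Analysed per arm | One-sided 5% (90% interval) | One-sided 2.5% (95% interval) |
|---|---|---|
| 306 | Φ(2.486 − 1.645) = 80.0% | Φ(2.486 − 1.96) = 70.1% |
| 360 | Φ(2.697 − 1.645) = 85.4% | Φ(2.697 − 1.96) = 76.9% |

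Exact binomial enumeration of the Wald interval at 306 per arm gives 80.3% and 70.1%, so the shortfall is not an artefact of the normal approximation.

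**3. Size needed for 80% power with a 95% interval.** 389 evaluable per arm (778 in total); 389 / 0.85 = 457.6, so 458 enrolled per arm (916 in total).

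**4. Where the two rules disagree.** At 306 per arm and rates near 45%, the 90% interval extends 1.645 × 4.02 = 6.6 points above the observed difference, and the 95% interval 1.96 × 4.02 = 7.9 points. Noninferiority therefore needs an observed excess on olive oil below 10 − 6.6 = 3.4 points in one case and below 10 − 7.9 = 2.1 points in the other. An observed excess between about 2.1 and 3.4 points is noninferior under one rule and not under the other.

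**The case against.** **A one-sided bound may have been meant.** The article never says two-sided or 2.5%, it calls its test one-sided, and its hypothesis statement in Methods/design speaks of a single bound. A one-sided 95% bound would be a 5% test with 80.0% power. This stands as a condition on the 70% figure. However, the text asks for intervals around risk reduction, number needed to treat and relative risk, and asks whether the interval includes delta. That naturally reads as two-sided. If a one-sided bound was intended, the text still has to say so.

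**The upper limit is not named.** Methods/design refers to the lower bound. Taken literally, requiring only the lower limit to be below 10% would almost always succeed for equal products (above 99.9% at 306 per arm). The 70.1% therefore assumes the conventional rule, in which the upper limit of olive oil minus HOFA must lie below the margin. The lower-bound wording is a separate defect. It does not remove the mismatch in error level, but any repair should cover it.

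**The sample size arithmetic is right.** This is correct on its own inputs. The fault lies in the pairing with the decision rule.

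**The error is conservative.** A two-sided 95% interval lowers the risk of a false noninferiority claim from 5% to 2.5%. That is true, but the loss falls on power, and the stated power is then wrong.

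**The shortfall depends on the 45% rate.** With 306 per arm and a 95% interval, the same formula gives power of 77% at an incidence of 30%, about 80% at 27% and 87% at 20%. So the gap narrows or closes at lower rates. But 45% is the article's own planning figure, and its 80% claim is made at that rate.

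**Conclusion.** The concern holds. With 45% incidence in both arms, a 10-point margin and 306 evaluable patients per arm, the stated 80% power belongs to a one-sided 5% test. Under the ordinary two-sided 95% interval, power is 70.1%, so the risk of missing noninferiority for truly equal products is about 30% rather than 20%. Since the per-protocol analysis is the main one, 306 per arm is the relevant number; even with no losses from the 720 enrolled, power is 76.9%. These figures rest on reading the 95% interval as two-sided and on comparing its upper limit with the margin. On the alternative reading, a one-sided 95% bound, power is 80.0%, but the article does not state that rule. On either reading the text needs correcting, because the primary decision must have a single error level.

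**What to change.** Choose one of the following before unblinding and use it consistently:

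- **Keep the two-sided 95% interval.** State in Sample selection that the decision is equivalent to a one-sided 2.5% test and that 306 evaluable per arm give about 70% power (about 77% if all 720 contribute).
- **Keep one-sided 5%.** State in Statistical analysis that noninferiority is judged on the upper limit of the two-sided 90% interval for the risk difference (olive oil minus HOFA). The 80% then stands, and 95% intervals can still be reported descriptively.

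In either case, name the same limit and level in the hypothesis statement in Methods/design, which now refers to the lower bound, so that the corrected sections do not contradict it.

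The cost is wording only. No patients are added and no trial procedure changes. Under the first option the stated power becomes less favourable. Under the second, the noninferiority claim openly carries a 5% one-sided error. Restoring 80% power with the 95% interval would instead take 916 enrolled, which neither option requires.

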## Discussion

Pressure ulcers are nowadays considered an important health issue causing a great economic impact by substantially increasing pharmaceutical expenditure. The total expenditure of pressure ulcer treatments amounts to 5% of annual health care expenditure and causes a higher health care burden on professional staff. This is a public health problem, which affects mainly older people, thus, this disease rate is increasing.

The acceptance of our hypothesis will provide evidence supporting the regular use of olive oil (nonoxygenated fatty acids) in the prevention of pressure ulcers in primary health care, likewise involving hospital care. Furthermore, owing to the lower price of the product, primary health care districts may consider purchasing them, owing to the reduction in health care workload for professional staff, as well as for the family caregivers, given that the incidence of pressure ulcers will be lower as well as the respective reduction in pharmaceutical expenditure.

The main limitation of the trial is that when performing the cost-effectiveness analysis, the variables on caregiver inputs may not be estimated, along with those variables regarding the expenditure derived from the patient’s suffering. Likewise, there might be a selection bias due to those patients who refuse to take part in the trial, which may involve differential baseline characteristics. For the purposes of this trial, in the analysis it will be taken into account whether there are differences among those who take part in the trial and those who do not. The same procedure will be applied for withdrawals during the follow-up period. The analysis will be carried out according to the protocol and intention to treat. In the event that the results of the two types of analysis do not match, the subgroup of patients who did not comply with the protocol will be studied, to determine the reasons before reaching a final conclusion of noninferiority.

The confusion bias derived from some variables such as age, sex, type of intervention, and nutritional status of the patient will be managed during the statistical analysis stage, by means of a multivariate analysis.

The usual application of olive-oil-based formulas may be helpful in preventing the appearance of any grade of pressure ulcer in immobilized patients, and thus, it will be a cheaper treatment and may be considered as an alternative treatment.

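### The cost model stops counting nurse visits when an ulcer appears and has no term for treating it, so the visit component of incremental cost favours the arm with more ulcers

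*Protocol article*

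**What the plan says.** All of the relevant rules stand in the protocol article under Methods/design, Sample selection.

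- **Exit at the ulcer.** The article states that "patients who develop grade 2 pressure ulcers with breaks in the skin are excluded from the trial", and of their later care: "Such patients will be treated again by the nurse who will cure the pressure ulcer, although this will be done out of the trial".
- **Product cost (NE).** This is the number of units needed for a full 112-day course, priced per unit. It does not shorten when an ulcer occurs.
- **Visit cost (VE).** The only variable cost is "the number of visits of the nurse to the patient’s home during the trial period", "which will act as a proxy measure of the level of care required".
- **Total cost.** CT = NE + VE. The text lists what is left out: structural fixed costs, family care, paid caregivers and intangible costs such as pain. Ulcer treatment is neither in the equation nor on that list.
- **End of assessment.** After baseline, "this will be repeated each week up to the conclusion of the follow-up period, or until a pressure ulcer appears in patients".

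Under Statistical analysis, these costs feed an incremental cost-effectiveness ratio with ulcer or no ulcer as the effect. The Discussion expects purchasers to be interested "owing to the reduction in health care workload for professional staff", on the ground that fewer ulcers will occur. Its stated cost limitations are caregiver inputs and patient suffering only.

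**The concern.** A proxy for care needed should rise when a patient gets worse. Here the rules combine to do the opposite. An ulcer-free patient can accrue visits for 16 weeks. A patient with an ulcer stops accruing them when nursing need increases. Because product cost is fixed, nothing elsewhere in CT offsets this.

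Counted visits are then negatively tied to the bad outcome by construction. Each ulcer prevented is booked as extra nursing cost, and the cost of the ulcer itself is valued at zero. Cost-effectiveness is the stated secondary objective. The workload saving anticipated in the Discussion is one that this model could not show even if it were real.

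**Working it through.** **Inputs from the protocol article (Sample selection):** horizon 16 weeks; weekly assessment until week 16 or the ulcer; assumed ulcer proportion 45% in each arm; margin 10 percentage points; 360 patients per arm after allowing for withdrawal.

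**Assumptions, not in the article:** one counted visit per week; ulcer detected at a weekly visit; onset either uniform over weeks 1 to 16 or at constant weekly hazard; the visit rate after an ulcer, varied from 1 to 3 per week.

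**The plan's own figures.** The article gives no expected visit count to reproduce. The sample size is used here only for scale: (1.645 + 0.842)² × 2 × 0.45 × 0.55 / 0.10² ≈ 306 per arm, and 306 / 0.85 = 360. Both agree with the text.

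**Step 1. Counted visits when counting stops at the ulcer.** With ulcer proportion p and mean week of ulcer m,

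mean visits = p × m + (1 − p) × 16.

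- Uniform onset: m = (1 + 16)/2 = 8.5, so mean visits = 16 − 7.5p.
- Constant hazard: h = 1 − (1 − p)^(1/16), which gives m = 7.71 at p = 0.45 and m = 7.45 at p = 0.55.

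| Ulcers | Uniform onset | Constant hazard |
|---|---|---|
| 35% | 13.38 | 13.18 |
| 45% | 12.62 | 12.27 |
| 55% | 11.88 | 11.30 |

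**Step 2. Difference between arms.**

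- An arm at 55% against one at 45%: −0.75 (uniform) to −0.97 (constant hazard) visits per patient. Times 360, this is about 270 to 350 visits not counted in the worse arm.
- An arm at 35% against one at 45%: +0.75 to +0.91 visits. The better arm is charged more.
- At low incidence, 15% against 5%: −0.75 to −0.78.
- Equal rates and equal timing: zero.

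**Step 3. The same comparison (55% against 45%) with visits counted to day 112 for everyone.** If patients receive v visits per week after an ulcer, the difference is (v − 1) times the absolute value in Step 2.

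| Visits per week after ulcer (assumed) | Uniform onset | Constant hazard |
|---|---|---|
| 1 | 0.00 | 0.00 |
| 2 | +0.75 | +0.97 |
| 3 | +1.50 | +1.94 |

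At weekly visits after the ulcer, full counting removes the artefact. At any higher rate it reverses the sign. These figures cover visits only; dressings and other treatment materials would come on top.

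**The case against.** The strongest counter-argument is that the article never says that the VE count stops at the ulcer. The trial period could mean 112 days for every patient, which would match the fixed window for product cost and is the reading under which VE works as a proxy. The remark that treatment takes place outside the trial comes where the text explains why the product can no longer be applied, and the stopping rule "or until a pressure ulcer appears in patients" governs assessments, not costs. This reading is possible. It is not the natural one: the patient is said to leave the trial, care is placed outside it, and no collection of later visits is described. Even if it is granted, CT still has no term for treatment materials, and the list of exclusions does not mention them.

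Other parts of the defence stand:

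- **Visit frequency is assumed.** VE is costed with the standard time of a community nurse's home visit, checked on 30 visits before the trial, which suggests routine care visits. The article does not support saying that most counted visits are study visits.
- **Total cost is not determined.** A reader might infer that the worse product will look cheaper overall. The documents do not show this, because CT also contains product cost and no unit prices are given. The result holds for the visit component.
- **At the planning assumption of 45% in both arms**, with similar timing, the between-arm bias is about zero.

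Two further defences are weaker. A narrow perspective that counts only the cost of prevention is legitimate if declared, but the article calls VE a measure of care required and does not declare ulcer care excluded. A condensed article may also leave detail to a fuller document, but here it prints the cost equation and its exclusions, so this is a stated rule.

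**Conclusion.** The point holds for the secondary cost-effectiveness endpoint. On the natural reading of the article, an ulcer shortens the counted visits and its treatment visits are not costed; on any reading, treatment materials are absent from total cost. The visit component then favours the arm with more ulcers, by about 0.75 to 0.97 visits per patient for a difference of the full 10-point margin (55% against 45%).

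The size rests on one visit per week and on uniform or constant-hazard onset. It shrinks to about zero as ulcer rates and timing become equal. The direction was the same for every pair of unequal ulcer rates tried. The article does not allow a statement about which product would look cheaper in total. The primary noninferiority comparison does not use these costs and is not touched.

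**What to change.** In the cost model:

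1. Define VE as nurse home visits from randomisation to day 112 for every randomised patient, whether or not an ulcer occurs.
2. Add to CT the visits and materials used for ulcer treatment up to day 112, taken from health-centre records, with treatment visits already in VE counted once.
3. Leave out visits made only for study assessment, or cost them equally over 16 weeks in both arms.

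Keep product cost on the fixed 112-day basis. Charging product only for days used may seem a natural companion change, but it would lower the counted cost of patients with ulcers and add to the same negative link.

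The cost is small: record extraction, over at most 16 weeks per patient, for those who develop an ulcer, by centres and nurses already taking part. It needs no new procedure and no change to patient care.

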The main role of the oil is its antioxidant function: for this purpose, the oil should have a low peroxide content and a high polyphenol content. Extra virgin olive oil includes 330 to 500 mg of polyphenols per kg of fat and less than 20 milliequivalent (mEq) weight of peroxide per kg of fat (the composition of the HOFAs includes from 40 to 50 mg of polyphenols per kg of fat and from 230 to 340 mEq of peroxide per kg of fat). Owing to its lipid composition, it is completely compatible with of human tissue cells, which means that its topical use does not cause allergy or irritation. Such properties lead us to consider a possible protective effect on the appearance of pressure ulcers, similar to those of HOFA, but at a much cheaper cost, as well as offering an alternative treatment option. Furthermore, there are no previous experiments with this product in the prevention of pressure ulcers in nursing care at home. The main aim of this trial is to assess whether the effectiveness of olive oil use is lower or higher than the HOFA in the prevention of pressure ulcers in immobilized patients receiving nursing care at home and, as a secondary aim, to assess the cost-effectiveness of this new intervention with regard to the use of HOFA.

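### The printed total-cost equation omits the unit price that the plan's own text says multiplies the number of containers, and it adds a container count to a visit count

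*Protocol article*

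**What the plan says.** The cost model is set out in the protocol article under Sample selection, in the paragraphs on secondary endpoints.

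- **Product cost, in words.** Treatment cost is the number of units NE_ij "multiplied by the price of one unit", written P_i and P_j. On the source of prices: "the price of each unit will be achieved from the information provided by each supplier according to the market price".
- **NE itself.** "The number of units will be the result of dividing the treatment period" of 112 days by the days one container lasts, printed as NE_ij = DT_ij/d_ij. Then: "The resulting amount achieved shall be rounded up, even if the whole number of units has not been fully used". NE is thus a whole number of containers.
- **Nurse visits.** VE is the number of home visits, "which will act as a proxy measure of the level of care required". Visit length is also to be obtained: "The mean time spent on each visit will be estimated" from health-district information and a timing exercise on 30 visits.
- **Total.** "the estimation of total costs (CT) in the model will remain as follows": CT_ij = NE_ij + VE_ij.

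Statistical analysis then calls for the incremental cost, the cost-effectiveness ratio of each treatment, the incremental cost-effectiveness ratio (ICER), and the cost of a 1% gain in successful prevention. The Background gives the economic motive: an effect similar to HOFA, "but at a much cheaper cost, as well as offering an alternative treatment option".

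**The concern.** The equation and the definitions just before it do not agree. Both terms in the equation are counts, of different things. The price, declared as an input and as a multiplier of NE, is absent. The visit time, which the study will take trouble to measure, is absent too. Both equations and all their symbols are legible, so this is not damage from text extraction.

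Cost-effectiveness is the stated secondary objective. An analyst who programs the equation as printed obtains a total that is not money, in which one container weighs the same as one nurse visit and the product price difference has no influence. Any incremental cost or ICER built on that total would be wrong.

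**Working it through.** The article states no cost figure, so there is nothing to reproduce. The check is one of units, followed by an illustration.

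**Units**

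- NE = 112/d, rounded up: containers.
- NE × P: money. This is the treatment cost as the text defines it.
- VE: visits. VE × visit time: hours. VE × visit time × cost per hour: money.
- CT as printed: containers + visits, which has no common unit.
- If NE in the total is read as shorthand for NE × P: money + visits. One visit then counts as one currency unit.

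**Illustration with equal use in both arms**

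From the document: 112 days, and rounding up. Assumed: d = 10, 14, 20 or 30 days per container; 16 visits (one per week); prices in arbitrary money units of 3 or 5 for olive oil and 6, 15 or 25 for HOFA.

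| d | NE | Printed CT = NE + 16, both arms | Printed difference | NE × (3 − 6) | NE × (3 − 15) | NE × (5 − 25) |
|---|---|---|---|---|---|---|
| 10 | 12 | 28 | 0 | -36 | -144 | -240 |
| 14 | 8 | 24 | 0 | -24 | -96 | -160 |
| 20 | 6 | 22 | 0 | -18 | -72 | -120 |
| 30 | 4 | 20 | 0 | -12 | -48 | -80 |

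The last three columns are olive oil minus HOFA with the price restored. The visit term cancels because visits are taken as equal.

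**Unequal container use**

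Suppose the olive-oil container lasts 14 days (NE = 8, price 3) and the HOFA container 20 days (NE = 6, price 15), with 16 visits each.

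- Printed: 24 − 22 = +2, so olive oil looks dearer.
- Priced: 8 × 3 − 6 × 15 = 24 − 90 = -66, so olive oil is cheaper.

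Unequal use therefore does not rescue the printed form; it can reverse the sign.

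**Unequal visits**

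Assume 0.5 hours per visit at 20 per hour. Each extra visit should then add 0.5 × 20 = 10. In the printed total, and also in NE × P + VE, it adds 1.

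**The case against.** The strongest reply is that this is a notation slip. The text defines product cost as units times price and names the source of the price, so NE in the total most naturally stands for that product cost. The Statistical analysis section refers to the increase in cost without citing CT, so it can be read with the correct definition. Most of this stands. A reader might infer that the olive-oil price cannot enter the result, or that the secondary objective cannot be answered. The text supports neither: price is a declared input, prices and visit times are to be collected, and the equation can be corrected at any time before the economic analysis.

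A reader might also take price as the only cost difference that the trial could show. That goes too far. Nurse visits are in the model as a variable cost, follow-up ends when an ulcer appears, and the Discussion expects less staff workload. Visits may therefore differ between arms. Days per container are also indexed by arm, so the exact zero in the illustration needs equal use and equal visits.

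Finally, a staff unit cost may sit in a fuller protocol that is not shown, so its absence from a journal article is no fault in itself. That is fair. But reading NE kindly repairs only the first term: the second is still a bare count added to money, in an equation presented as the total cost, and the measured visit time has no place in it.

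**Conclusion.** The point holds as a contradiction between an equation and the text that defines its terms. As printed, CT adds containers to visits, leaves out the declared price and the visit time, and does not reflect the product price difference. The text itself supplies the correction for the product term.

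The size is not determinable from the document. Under the assumed container lives, prices and equal visits, the error in the incremental cost is 12 to 240 money units per patient, which is the whole product price difference. Other inputs would give other figures; only the missing price and the mixed units do not depend on them. Price is a main expected cost difference, not the only possible one. The primary endpoint and its noninferiority analysis are unaffected.

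**What to change.** Replace the equation by

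CT_ij = NE_ij × P + VE_ij × (mean visit time × nurse cost per unit time),

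with P the price for the arm concerned and NE rounded up as already stated. Name the source of the nurse cost. In Statistical analysis, state that the incremental cost and the ICER are computed from this monetary CT.

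The cost is small: a change of formula and wording, with no change to design or sample size. Prices and visit time are already to be collected. The one new item is a staff unit cost, which could be requested from the health districts that supply the visit time. It should be fixed before the economic analysis, so that the value of a visit is not chosen with results in view.
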